## Abstract

**Introduction:** The On&Out study is aimed at assessing the effectiveness, cost-utility and physiological underpinnings of the FIBROWALK multicomponent intervention conducted in two different settings: online (FIBRO-On) or outdoors (FIBRO-Out). Both interventions have proved to be efficacious in the short-term but there is no study assessing their comparative effectiveness nor their long-term effects. For the first time, this study will also evaluate the cost-utility (6-month time-horizon) and the effects on immune-inflammatory biomarkers and Brain-Derived Neurotrophic Factor (BDNF) levels of both interventions. The objectives of this 6-month, randomized, controlled trial (RCT) are 1) to examine the effectiveness and cost-utility of adding FIBRO-On or FIBRO-Out to Treatment-As-Usual (TAU) for individuals with fibromyalgia (FM); 2) to identify pre–post differences in blood biomarker levels in the three study arms and 3) to analyze the role of process variables as mediators of 6-month follow-up clinical outcomes.

**Methods and analysis:** Participants will be 225 individuals with FM recruited at Vall d’Hebron University Hospital (Barcelona, Spain), randomly allocated to one of the three study arms: TAU vs. TAU + FIBRO-On vs. TAU + FIBRO-Out. A comprehensive assessment to collect functional impairment, pain, fatigue, depressive and anxiety symptoms, perceived stress, central sensitization, physical function, sleep quality, perceived cognitive dysfunction, kinesiophobia, pain catastrophizing, psychological inflexibility in pain and pain knowledge will be conducted pre-intervention, at 6 weeks, post-intervention (12 weeks), and at 6-month follow-up. Changes in immune-inflammatory biomarkers [i.e., IL-6, CXCL8, IL-17A, IL-4, IL-10, and high-sensitivity C-reactive protein (hs-CRP)] and Brain-Derived Neurotrophic Factor will be evaluated in 40 participants in each treatment arm (total n = 120) at pre- and post-treatment. Quality of life and direct and indirect costs will be evaluated at baseline and at 6-month follow-up. Linear mixed-effects regression models using restricted maximum likelihood, mediational models and a full economic evaluation applying bootstrapping techniques, acceptability curves and sensitivity analyses will be computed.

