### 2.3 Sample size calculation

Two-hundred and twenty-five individuals who meet the selection criteria for the study will be recruited. The estimated sample size needed is n = 63 participants per condition considering a moderate effect size (Cohen’s d = 0.5) for the difference between the active arms at post-intervention compared to the control group for the primary variable (i.e., FIQR score) with an alpha = 0.05 and 1-b power = 0.80. With an expected dropout rate of 20%–25%, the final sample size is estimated at 75 individuals per arm. The effect size used for the sample size calculation corresponds to the average effect size for multicomponent interventions in FM vs. control group (Nüesch et al., 2013). Previous RCTs evaluating the FIBROWALK intervention indicated effect sizes between d = 0.4 (Serrat et al., 2021a) and d = 1.83 (Serrat et al., 2020). Using as a reference previous studies of the group evaluating the effect of different non-pharmacological treatments in FM patients on blood values of immuno-inflammatory markers (Andrés-Rodríguez et al., 2019; Montero-Marin et al., 2020), it is estimated that a sample size of 40 subjects per arm will be sufficient to be able to detect changes in the evaluated variables.

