#### 2.11.1 Analysis of clinical effectiveness

The primary effectiveness analysis will be conducted on an intention-to-treat (ITT) basis with the FIQR total score as a primary clinical endpoint (McCoy, 2017) and by linear mixed-effects regressions with restricted maximum likelihood (REML). REML accounts for the correlation between repeated measures for each individual and produces less biased estimates of variance parameters when using small sample sizes or unbalanced data (Egbewale et al., 2014). No imputation of missing data will be conducted, since it has been reported that multiple imputation is not necessary for all types of missing data (missing completely at random, missing at random, and missing not at random) before computing longitudinal mixed model analysis (Twisk et al., 2013). Unstandardized regression coefficients (B) and 95% confidence intervals (95% CIs) will be computed for the ‘group x time’ interaction between groups at 6-week, post-treatment and 6-month follow-up assessments. Cohen’s d will be calculated for each pairwise comparison, using the pooled baseline SD to weight the differences in the pre–post mean values and to correct for the population estimate (Morris, 2008). The rule of thumb for effect size interpretation will be the classical cutoffs for Cohen’s d of 0.20 = small, 0.50 = medium, and 0.80 = large. All secondary clinical endpoints will be analyzed using the same statistical procedure. Benjamini–Hochberg correction for multiple comparisons will be applied to control for false rate discovery (Glickman et al., 2014). All the analyses will be replicated using a “completers” approach including all participants who finished the study, and a per-protocol approach, taking into account only those patients who attended at least 75% of the sessions (9 out of 12).

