#### 2.11.4 Analysis of changes in biomarkers

The effect of interventions on immune-inflammatory markers and BDNF levels will be evaluated also with REML. In those cases where cytokine concentrations are under detection level of the test, the detection limit value will be assigned. Cytokines, hs-CRP and BDNF values will be subjected to a natural logarithmic transformation to normalize the significantly skewed data distributions. In order to comprehensively integrate pro-inflammatory with anti-inflammatory markers, indexes indicative of inflammatory balance will be calculated (e.g., IL-6/IL-10, CXCL8/IL-10 and hs-CRP/IL-10) in a similar way to previous studies (Andrés-Rodríguez et al., 2019). Since some pharmacological treatments such as antidepressants are reported to potentially affect some cytokine levels (Hannestad et al., 2011), differences in such levels between patients taking vs. not taking these drugs will be also evaluated. In case of any statistically significant effect, antidepressant status (“taking” = 1, “not taking” = 0) will also be included as a co-variable in the REML analyses for each specific biomarker.

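### Antidepressant adjustment of each biomarker model depends on a significance test of levels, and the co-variable it adds barely touches the pre–post treatment contrast

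*Protocol article*

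**What the plan says.** Section 2.11.4 of the protocol article sets the biomarker model: "The effect of interventions on immune-inflammatory markers and BDNF levels will be evaluated also with REML". Because antidepressants may affect some cytokines, "differences in such levels between patients taking vs. not taking these drugs will be also evaluated". The result decides the model. "In case of any statistically significant effect, antidepressant status", coded 1 or 0, "will also be included as a co-variable in the REML analyses for each specific biomarker". The section gives no alpha, time point or taker share for this comparison, and names no interaction term.

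The target of the mixed models is described in section 2.11.1 for the clinical outcomes: the group x time "interaction between groups at 6-week, post-treatment and 6-month follow-up assessments". Section 2.11.4 carries the method over with the word also, and its title and the second study objective both concern pre–post change.

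The Abstract fixes the size of the substudy: markers "will be evaluated in 40 participants in each treatment arm (total n = 120) at pre- and post-treatment". Section 2.7 asks participants to keep their medication regimen for the six months. Section 2.8 lists current medication under clinical data, which Table 3 marks at baseline only. In practice, antidepressant status is a fixed baseline variable.

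**The concern.** There are two weaknesses in the rule.

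First, a non-significant comparison in a modest sample leads to no adjustment, separately for each marker. Which models carry the term is then partly a matter of chance.

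Second, the test and the adjustment concern levels, while the treatment effect is a contrast of changes. A covariate that is constant within a person and enters as a main effect drops out of that contrast when both samples are present. The feature of antidepressant use that could disturb the contrast is a different change among takers, combined with an unequal share of takers across arms of 40. The rule, read plainly, adds no term for that.

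The stake is a report that says antidepressant use was controlled for when the pre–post treatment estimate is in effect unadjusted. A modest opportunity to absorb chance imbalance is also lost.

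**Working it through.** **Inputs.** From the documents: 120 women, 40 per arm, two visits (Abstract); "alpha = 0.05 and 1-b power = 0.80" and a 20–25% dropout rate (section 2.3, stated for the FIQR and the main trial); medication held constant and recorded at baseline (sections 2.7 and 2.8, Table 3). Assumed, because the documents do not give them: two-sided 0.05 for the antidepressant comparison, a 0.5-SD difference, and 20–50% takers.

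**The plan's own figure.** The documents give no calculation for the antidepressant comparison. The one available check is the FIQR sample size, "considering a moderate effect size" of d = 0.5: n = 2(1.960 + 0.842)² / 0.5² = 62.8, so 63 per arm, as stated. The same formula family is used below.

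**Step 1: how often the test misses a 0.5-SD level difference.** Miss rate = 1 − Φ(0.5·√(n₁n₂/N) − 1.960). For 60 v 60: 0.5·√30 = 2.739, Φ(0.779) = 0.782, miss 21.8%. For 24 v 96: 0.5·√19.2 = 2.191, Φ(0.231) = 0.591, miss 40.9%. After dropout, N = 120 × 0.80 = 96 or 120 × 0.75 = 90.

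| N | 50% takers | 30% takers | 20% takers |
|---|---|---|---|
| 120 | 21.8% (22.5%) | 29.1% (29.8%) | 40.9% (41.6%) |
| 96 | 31.2% (32.1%) | 38.8% (39.7%) | 50.0% (50.8%) |
| 90 | 34.0% (35.0%) | 41.5% (42.5%) | 52.5% (53.3%) |

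Noncentral-t values are in brackets. With all 120 women the range is about 22–42%. About 52% is reached only with post-dropout numbers and 20% takers.

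**Step 2: chance firing across markers.** If no marker truly differs and the tests were independent, at least one would fire with probability 1 − 0.95⁵ = 23% (the five cytokines) or 1 − 0.95⁷ = 30% (adding hs-CRP and BDNF). Correlated markers would lower this.

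**Step 3: what the added term does.** Let A be the fixed 0/1 status, u the person effect, and τ the arm-specific change.

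- Before: y₀ = α_arm + βA + u + e₀
- After: y₁ = α_arm + τ_arm + βA + u + e₁
- Change: y₁ − y₀ = τ_arm + e₁ − e₀

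βA cancels, whatever β is. In 100 simulated trials per setting (40 per arm, random-intercept REML, total SD 1, β = 0.5), adding the main effect moved the group x time estimate as follows:

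- Complete pairs: at most 4 × 10⁻¹⁵; standard error 0.206 with and without the term.
- 25% of post samples missing: mean 0.011, maximum 0.049; standard error 0.233 both ways. The mean shift is 0.011/0.233 = 0.05 standard errors. A separate run of 40 data sets with 22.5% missing gave a mean of 0.02 SD.
- Status allowed to vary over time (15% switching assumed): mean 0.032, maximum 0.137. This setting departs from the instruction to hold medication constant and from the baseline-only recording.

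**Step 4: what a useful adjustment could gain.** If takers change differently by γ, the contrast between two arms carries γ(p₁ − p₂), where p is the taker share in each arm. With γ = 0.5 SD, 50% takers and 40 per arm, the SD of p₁ − p₂ is √(2 × 0.25/40) = 0.112. The mean absolute difference is 0.798 × 0.112 = 0.089, and 0.5 × 0.089 = 0.045 SD. Simulation with the antidepressant x time term gave a mean shift of about 0.05 SD (largest 0.18) and a standard error about 3% smaller. Against a standard error near 0.21, 0.05 is roughly a quarter of one standard error.

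**The case against.** The strongest reply is that the two weaknesses offset each other. If the added term is almost inert, leaving it out after a missed test costs almost nothing. That stands for the treatment estimate: the miss rate shows that the rule is unstable, and it does not measure harm. It does not rescue the rule, because the change contrast goes essentially unadjusted whichever way the test falls.

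Other points also stand and limit what can be said:

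- A reader might infer that the biomarker treatment effects are biased. Allocation is randomised, so omitting a baseline covariate does not bias the arm contrast in expectation. Nothing in the documents says takers change differently.
- A reader might infer that the co-variable can never alter the estimate. That is exact only for complete pairs, fixed status and free baseline arm means. The trial expects dropout, and small shifts then occur.
- A reader might infer that a different change among takers can never be detected by a level comparison. That holds only if baseline levels alone are tested, when the rule fires about 5% of the time. If post levels are tested, a 0.5-SD difference in change appears as a 0.5-SD level difference. With 93 patients the rule then fires about 48–67% of the time. The section gives no time point. Even then, a main effect would not model the difference in change.
- Main effect only is an inference from the word co-variable; the text neither states nor excludes an interaction.

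The missing alpha, time point and exact model terms are details that an article may leave to a fuller document, and they are not counted against the plan. The significance gate itself is stated in the article.

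**Conclusion.** The point holds as a minor one about method. Section 2.11.4 lets a significance test on levels choose the covariate for each biomarker. With at most 120 women that test would miss a 0.5-SD difference about 22–42% of the time, rising to about 52% on post-dropout samples with 20% takers. These rates rest on an assumed effect size, alpha and taker share. On the plain reading, the term that the test admits does nothing to the pre–post treatment contrast with complete pairs, and moves it by about 0.01–0.02 SD on average with 20–25% missing.

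The consequences are models that differ between markers partly by chance and an apparent control for antidepressants that the change estimate does not contain. The documents do not support a claim of biased treatment effects. The expected gain from doing better is small: about 0.05 SD average shift and 3% in standard error, and that only if takers change differently by an assumed 0.5 SD.

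**What to change.** Delete the significance pre-test in section 2.11.4. For every biomarker, prespecify antidepressant status as recorded at baseline, together with its interaction with time, in the REML model. The comparison of levels between takers and non-takers can stay as a description that does not decide the model.

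A baseline-adjusted model of the post value (post on baseline biomarker, antidepressant status and arm) is an alternative. It is not equivalent: it estimates the slope on baseline where the group x time model contrasts changes, and it leaves out participants without a post sample. If it is preferred, it should be named as the model in advance.

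The cost is a change of wording and one or two degrees of freedom per model. The data are already collected at baseline, and nothing in the conduct of the trial changes.

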### 2.12 Ethical issues of the project

Written informed consent will be obtained from all participants prior to randomization. Participants will be provided with a general overview of the aims and characteristics of the study and the interventions before signing the informed consent. They will also be assured that they will be participating voluntarily and can withdraw at any time from the study with the guarantee that they will continue to receive the most appropriate medical treatment prescribed by their general practitioner. The study will be conducted in compliance with the Declaration of Helsinki (version in force; currently Fortaleza, Brazil, October 2013). The study will be conducted in accordance with the protocol and with the relevant legal requirements: Law 14/2007 of July 3, on Biomedical Research. The VHIR Research Committee Board evaluated and approved the study protocol in May 2022 [PR (AG)99/2022]. All patient data will be treated as confidential and only the research team will be allowed to access it after recodification of name and personal identity number (so no individual can be directly identified). Only the principal investigator ([name]) and the clinician coordinator of the study (MS) will have access to the code key which will be stored separately in a safe place in accordance with Spanish legislation. All data will be computer processed and stored. Blood samples will be stored encrypted, and will not be directly traceable back to individuals. Blood samples will be used only in ways to which the participants consented and may only be made available to a new research project after Ethical Research Committee approval and participants provide a new agreement. Furthermore, the participants have the right to request, without explanation, that their samples be destroyed or made completely anonymous.

### 2.13 Blinding

Randomization and group allocation will be completely masked for the study assessors and study participants will be asked not to communicate with the assessor about the treatment received. The study participants will be provided with a summary of evidence of the FIBROWALK program which constitute the basis for FIBRO-On and FIBRO-Out programs. As it is usual in non-pharmacological trials, neither participants nor the therapists can be blinded to treatment allocation. The therapists in the FIBRO-On and FIBRO-Out arms will not be involved in any assessment task of the study.

### 2.14 Forecast execution dates

Initial recruitment of patients: September 2022.

Finalization of patient recruitment: January 2023.

Finalization of patient monitoring period: July 2023.

Publication of results: December 2023.

## 3 Discussion

The On&Out study will evaluate the effectiveness, cost-utility and the physiological effects of adding the FIBROWALK program in Online (i.e., FIBRO-On) or in Outdoor format (i.e., FIBRO-Out) to TAU. In order to determine the mechanisms of action of these interventions, we will also evaluate potential process measures of these interventions, as well as physiological markers with evidence of alteration in FM and that are likely modifiable by non-pharmacological interventions. Three previous studies evidenced the short-term efficacy (i.e., post-intervention) compared to TAU of both the FIBRO-On (Serrat et al., 2021a; Serrat et al., 2022b) and FIBRO-Out programs (Serrat et al., 2020); however, the present RCT will evaluate for the first time if these clinical effects are maintained at 6-month follow-up along with the aforementioned analyses on cost-utility, mediation and physiological markers.

The fact that FIBROWALK’s tested interventions are in online format (FIBRO-On) or in group format (FIBRO-Out) can make them more cost-effective, and therefore of interest for health managers. Additionally, both formats can be considered “safe” in epidemiological terms (compared to face-to-face indoor classical interventions) as they do not imply in closed spaces shared with other people where exists a higher risk for contagion (e.g., Bazant and Bush, 2021). Furthermore, particularly for the FIBRO-On intervention, these therapies can also be followed under strict social distancing measures and even in lockdown circumstances. If the results of this RCT are strong enough in terms of efficacy and cost-utility, FIBRO-Out and/or FIBRO-On could be considered for their inclusion in the public healthcare Spanish system to treat individuals suffering from FM. Additionally, this RCT may also pave the way for further RCTs testing the efficacy of these interventions in other chronic diseases cursing with central sensitization (e.g., irritable bowel syndrome, chronic headache, temporomandibular disorder, pelvic pain syndromes), along with other emerging conditions such as persistent post-COVID syndrome which may display overlapped symptoms with FM (Haider et al., 2022).

The On&Out study will also evaluate the effect of the FIBROWALK multicomponent programs on immuno-inflammatory markers and BDNF levels that seem to be altered in FM and/or play a role in the effectiveness of non-pharmacological treatments (Rodriguez-Pintó et al., 2014; Andrés-Rodríguez et al., 2019; Montero-Marin et al., 2019). It should also be noted that, to date, the effect of any multicomponent program on such biomarkers in FM has not been evaluated by means of a RCT design. Furthermore, the evaluation of changes in these biomarkers and their association with clinical change will further deepen the understanding of the role of the immune system and neuroprotective agents in FM and related disorders cursing with central sensitization. Associated with this substudy of the project, it should be noted that the inclusion of biomarkers may also make it possible to determine different patient profiles (based on their psychobiological characteristics) which could be predictive of a greater or lesser response to the treatments under study. This aspect is fully connected with the emerging field of personalized treatments and can contribute to optimizing the use of healthcare services while also enhancing the efficacy and cost-effectiveness of the interventions evaluated (Thase, 2014; Lopresti, 2017; Carvalho et al., 2019).

This study has some strengths that should be highlighted. The inclusion of a relatively large sample and of a comprehensive set of measures will allow us to compare the short term (pre-post) and long-term (6 months) effectiveness of two different formats of the FIBROWALK multicomponent program on core FM outcomes and psychological process measures. Furthermore, the identification of cost-effective interventions is a priority for the national health system, especially for highly prevalent conditions such as FM. This study will evaluate for the first time the cost-effectiveness of two formats (which can be particularly useful in the pandemic and post-pandemic era) of a multicomponent intervention for FM. In this sense, it is necessary to introduce new practices in the provision of healthcare services to improve efficiency in the use of resources. In this regard, boosting treatments aimed at changing lifestyles and patterns of cognition and behavior (as it is aimed in FIBROWALK) constitutes a strategy of financial sustainability as, in the long-term, it will allow an extension of the culture of health understood holistically and, therefore, a decrease in the burden of disease on society as a whole. Our study will also explore immune-inflammatory and neuroprotective pathways behind the efficacy of the evaluated treatments, and will combine clinical and process measures which may lead to a better characterization of the syndrome, to new therapeutic interventions, and to a better prediction of treatment response in order to better determine what works for whom in the field of personalized medicine. Finally, it is also worth mentioning that the present RCT will involve six therapists (three psychologists and three physiotherapists) in delivering the FIBRO-Out intervention; doing so (instead of only one therapist delivering the therapy) can provide more realistic and generalizable results (Ost, 2014) which can be useful for the future implementation of these interventions in healthcare systems.

There are also some potential limitations that should also be recognized in this RCT. One of the main risks of this project may be dropouts and non-adherence, which are expected to be higher than in previous studies that only evaluated the short-term efficacy of the interventions (Serrat et al., 2020; Serrat et al., 2021a; Serrat et al., 2021b; Serrat et al., 2022b). In this regard, since previous studies showed very high adherence to the programs (over 90%; Serrat et al., 2020; Serrat et al., 2022b), a dramatically high dropout in the present study is not expected; however, to limit the effect of these dropouts and lack of adherence in our results, we will conduct several sensitivity analyses (ITT, completers, per protocol analysis). We also have to note the lack of blinding of participants and therapists, which is a typical bias in any RCT including non-pharmacological treatments. Although a weekly questionnaire will be administered to check the adherence to FIBRO-On program (i.e., watching the videos), there is a risk that some participants in the FIBRO-On group do not watch the videos and inform differently. It is also relevant to highlight that this RCT will be carried out in a specialized unit of tertiary referral hospital in the context of clinical practice. Related to this, stricter inclusion/exclusion criteria could not be established due to pressures in daily clinical practice (i.e., most patients will be admitted). At the same time, this latter point may have a positive aspect by increasing the external validity of the study and so the generalization of the results into the “real” clinical practice.

Up to date, there is no study assessing the cost-effectiveness of multicomponent approaches for FM neither evaluating the long-term effectiveness of such type of interventions in online or outdoor formats. If one or both treatments evaluated in this present RCT (i.e., FIBRO-On and/or FIBRO-Out) shows to be effective and cost-effective they should be included as part of the standard of care for treating FM. Furthermore, since both interventions are, per definition, conducted out of the hospital settings, they could also be safely administered in the context of future pandemics, and (in the particular case of the FIBRO-On program) in circumstances of low accessibility to effective treatments for FM (e.g., in remote areas), highly congested healthcare services and/or low availability of clinical resources. The On&Out project is also aimed at determining psychophysiological patient profiles which can be useful for identifying potential treatment beneficiaries (i.e., treatment responders) beforehand which may in turn improve healthcare resources allocation. Last but not least, the present study may also help us in deepening our knowledge on which psychological and physiological mechanisms underpin the clinical effects of non-pharmacological interventions in FM, further contributing to the potential detection of novel therapeutic targets.

